#### Maximal voluntary isometric contractions

We use a specially prepared measuring device with a dynamometer attached to stiff band metal chains, prepared similarly to those in Roussel et al. and Essendrop et al. [38, 39]. The ICC for a similar device, used by one of the senior authors for lumbar muscle strength assessment, is > 0.94. For the assessment of maximal isometric strength, a maximal voluntary isometric contraction for 6 s is used. The same procedure of obtaining a maximal voluntary contraction is used for every strength measure. Movement is assessed in 3 planes for the trunk (extension, left and right abduction) and operated hip (flexion, extension, and abduction), and movement is assessed in 2 planes for the contralateral hip (extension, abduction). All strength tests are performed in a neutral standing position, and the patient rotates on the measuring device so that the exerted force is always in the direction opposite of the dynamometer. Before the measurements, the height of pelvic support is set to the reference point of the iliac crest of each patient. Patients are verbally encouraged to generate maximal effort. The mean duration of the complete test is 20 min. We wrap the band around the trunk under the armpits for trunk tests and around the ankle for leg tests. We measure the height of pelvic support, maximal contraction force, and distance between the upper border of the support board and the middle point of the stiff band. All measurements are taken twice.

#### Questionnaires

##### Harris Hip Score

The HHS is a widely used disease-specific measure of hip disabilities after THA. The physiotherapist administers the test in the form of a structured interview with the patients. The domains include pain, functions of daily living, and gait. The rating scale is from 0 (worse) to 100 points (best) [40]. The HHS is considered to have good validity and reliability [41].

##### 36-Item Short Form Health Survey

The SF-36 Health Survey was first made available in standard form in 1990. The eight health domains represented in the profile were selected from the 40 domains that were included in the Medical Outcome Study (MOS) by Stewart and Ware [42]. The RAND 36-Item Health Survey (version 1.0) is a set of generic, coherent, and easily administered quality-of-life measures. It taps eight health concepts: physical functioning, bodily pain, role limitations due to physical health problems, role limitations due to personal or emotional problems, emotional well-being, social functioning, energy/fatigue, and general health perceptions. It also includes a single item that provides an indication of perceived change in health [43]. These 36 items, presented in RAND 36-Item Health Survey 1.0, are identical to the MOS SF-36 described in Ware and Sherbourne [44]. Scoring of the RAND 36-Item Health Survey 1.0 is clearly described in scoring instructions [43]. The survey is a practical, reliable, and valid measure of physical and mental health. In our study, we will use the Slovenian translated and validated version by Marn-Vukadinović et al. [45].

#### Training compliance

All participants in both groups will keep a training diary concerning all training activities; they will make marks by every exercise they perform on each day, write notes if they will perform any other sport activities (walking, stationary bicycling, and others), note any adverse effects, and note reasons for skipped training exercises if applicable. They will also record their pain level by using the visual analog scale (VAS) [46] during the day, before and after training, and during the night. All these information will be used to draw conclusions about patient satisfaction, feasibility, and safety of the protocols.

### Data management and analysis

All data will be collected and stored in paper form by the corresponding author, who is responsible for the confidentiality of the data. All check-up forms will be printed and completed preoperatively and at every check-up by the physiotherapist and orthopedic surgeon. The questionnaires will also be printed and completed by patients. The corresponding author will enter the data into anonymized tables, which will then be used for statistical processing. The software program SPSS 21 (IBM SPSS Statistics for Windows, version 21.0. Armonk, NY: IBM Corp.) will be used for statistical analysis.

We will perform an intention-to-treat (ITT) analysis, which is an analytic strategy for reducing potential bias in treatment effects arising from missing data in randomized controlled trials. In ITT analysis, a study participant is analyzed as belonging to whatever treatment group he/she was randomized into, whether or not the treatment course was completed as intended. In case of missing data, sensitivity analyses will be performed and reported.

Before any statistical analysis, data will be tested for normal distribution using the Kolmogorov–Smirnov test (K–S test). With normally distributed variables, the analysis of variance for repeated measures (AnovaRM) with two factors (time × group) will be employed. It will test the differences in the effects of two different exercise protocols. AnovaRM will be used to analyze between-group differences in the score changes among all time points, represented by preoperative measurements (on admission to the hospital) and measurements 1, 3, and 12 months postoperatively. Afterwards, the initial AnovaRM, post hoc tests with AnovaRM (time × group) with two time points will be performed. Differences between all pairs of time points will be analyzed. Additionally, the paired samples *t*-test to test for in-group differences in the score changes between the pairs of time points and the independent samples *t*-test for between-group comparisons at the same time point will be calculated. The bivariate Pearson correlation will be calculated for testing the relationships between variables representing relative changes in the results between two different time points (e.g., post-treatment/baseline) for each group separately. To test the reliability of maximal voluntary isometric contraction measurements and the 8UG test, we will use the intraclass correlation coefficient (ICC) with the two-way mixed-effects model with absolute agreement. Data will be presented as the arithmetic mean and standard deviation. In the case of a non-normal distribution, data will be presented as the median and interquartile range, and nonparametric tests will be used respectively for comparisons of dependent and independent groups. Instead of AnovaRM, the nonparametric marginal model (nparLD, R-statistics) [47] will be used. T-tests for dependent and independent samples will be changed with Wilcoxon matched-pair signed-rank test and Mann–Whitney *U* test, respectively. The Pearson correlation will be substituted with the Spearman rank correlation. Adverse effects comparison among the two groups will be made by using the chi-square test. We will consider a *P* value less than 0.05 as significant for all measures and use a 95% confidence interval (CI). A significance level (alpha) of 0.05 will be tested with a two-tailed test.

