### Objectives

The primary objective of our study is to evaluate the efficacy of an early postoperative home-based strength training protocol — to assess whether it can improve patient functional outcomes at 3 months and 1 year following surgery. The secondary objectives are the feasibility of the presented protocol for all elective THA patients and its safety.

Our study also aims to assess patient satisfaction with enhanced targeted physiotherapy and to prepare a new standardized rehabilitation protocol with videos that will be effective, safe, and accessible to all THA patients.

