
### Outcome measures

The primary outcome of the study is the efficacy of the chosen protocol, measured by physical tests. These comprise the 10 MW test, the 8-foot Up and Go (8UG) test, and isometric muscle strength. Secondary outcomes are the patient questionnaires, which will be used to draw conclusions about patient satisfaction and the feasibility of the protocols, and consistent recording of any adverse effects.

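### The first-line test is a directionless four-visit time × group interaction, and the planned contrasts that answer the 3- and 12-month objective have no precedence over it

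*Protocol article*

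**What the plan says.** The Objectives section of the protocol article gives the primary aim as efficacy: "to assess whether it can improve patient functional outcomes at 3 months and 1 year following surgery". Under Outcome measures, "The primary outcome of the study is the efficacy of the chosen protocol, measured by physical tests"; these are the 10-m walk, the 8-foot Up and Go and isometric strength.

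The Data management and analysis section then lays out the tests in this order:

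- A two-factor (time × group) repeated-measures ANOVA comes first. Its purpose is stated: "It will test the differences in the effects of two different exercise protocols". Its scope is stated too: "AnovaRM will be used to analyze between-group differences in the score changes among all time points", that is, the preoperative assessment and "measurements 1, 3, and 12 months postoperatively".
- After it, "post hoc tests with AnovaRM (time × group) with two time points will be performed", and "Differences between all pairs of time points will be analyzed".
- An independent-samples t-test "for between-group comparisons at the same time point will be calculated".
- P below 0.05, two-sided, counts as significant for all measures.

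No visit and no contrast is named as the one that decides efficacy. The rank-based fallback for non-normal data replaces the ANOVA with a model of the same kind and names no target contrast either. The Discussion predicts the largest difference at 3 months.

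**The concern.** The objective asks a directional question at two visits: is the intervention arm better at 3 months, and at 12 months? The null of the four-visit interaction is different: that the mean profiles of the two arms are parallel across all four visits. It is rejected by any departure from parallel, at any visit and in either direction. A significant result therefore does not show where the arms differ or which arm is better.

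Most of the post hoc set has a related problem. Four visits give six pairs, and only baseline–3 and baseline–12 months address the objective. Baseline–1 concerns early recovery. The 1–3, 1–12 and 3–12 month pairs compare postoperative slopes. If the intervention arm lags at 1 month and has caught up by 3 months, the 1–3 and 1–12 pairs credit it with the larger improvement although neither target visit shows benefit.

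At stake is which P value may be cited as the trial's efficacy result. The misalignment arises with a single outcome such as gait speed, so dividing alpha among the existing tests would not cure it.

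**Working it through.** **Inputs from the protocol article.** From the sample size section: difference 0.10 m/s, SD 0.28 m/s, two-sided 5%, power 80%, 124 per group. From the analysis section: four visits, time × group.

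**Assumptions.** The correlation r between visits is not given; it is taken as exchangeable, 0.3 to 0.8. Data are taken as complete.

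**The plan's own figure.** n per group = 2 × (1.960 + 0.842)² × 0.28² / 0.10² = 2 × 7.85 × 7.84 ≈ 123.1, rounded up to 124. Power at 124 is 80.3%. The stated size is correct, but for one two-group comparison, not for the interaction.

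**Scenario.** The intervention arm is 0.10 m/s slower at 1 month only; the arms are equal at baseline, 3 and 12 months.

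**Omnibus test.** The between-arm differences are (0, −0.10, 0, 0), with mean −0.025. Deviations from that mean are (0.025, −0.075, 0.025, 0.025), and their squares sum to 0.0075. The noncentrality is

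λ = (124/2) × 0.0075 / [0.28² × (1 − r)] = 0.465 / [0.0784 × (1 − r)],

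referred to F with 3 and 3 × 246 = 738 degrees of freedom.

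**Two-visit pair containing month 1** (baseline–1, 1–3 or 1–12):

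z = 0.10 / [0.28 × √(2(1 − r)) × √(2/124)].

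| r | λ | Omnibus significant | z | Each month-1 pair significant |
|---|---|---|---|---|
| 0.3 | 8.47 | 68% | 2.38 | 66% |
| 0.5 | 11.86 | 83% | 2.81 | 80% |
| 0.7 | 19.77 | 97% | 3.63 | 95% |
| 0.8 | 29.66 | 99.8% | 4.45 | 99% |

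In the 1–3 and 1–12 pairs the significant result favours the intervention, because that arm catches up.

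**Simulation check** (6,000 trials each at r = 0.5 and 0.7). The omnibus rejects in 83.2% and 97.4%. The baseline–3 and baseline–12 pairs and the t-tests at 3 and 12 months each reject in 4.8% to 5.4%. At least one of the baseline–3 and baseline–12 pairs rejects in about 9%. With autoregressive correlation 0.7 (2,000 trials) the omnibus rejects in 93% and the 1–3 pair in 95%. With no difference at any visit the omnibus rejects in about 5%, so it is valid for its own null.

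**Smaller deficit.** With 0.05 m/s at 1 month only and r = 0.5 to 0.7, the omnibus rejects in 27% to 43% and the 1–3 and 1–12 pairs in 29% to 44% each.

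**What the omnibus cannot separate.** λ depends only on squared deviations. A 0.10 m/s harm at 1 month only, a benefit of that size at 1 month only, one at 3 months only, and one sustained at 1, 3 and 12 months all give a sum of 0.0075. The rejection rate is therefore the same for all four: 83% at r = 0.5.

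**The case against.** The strongest reply is that the right tests are already in the plan. The baseline–3 and baseline–12 pairs and the same-visit t-tests are all prescribed, and they hold at about 5% in the scenario above. An omnibus test followed by pairwise tests that locate the difference is conventional. All of this stands.

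A reader might infer that the trial will declare efficacy whenever the omnibus test or a slope pair is significant. The document does not support that: no sentence attaches an efficacy conclusion to either. Nor does it support reading the omnibus as a gate. The post hoc tests follow it without any condition that it be significant, so a weak omnibus result would not block the 3-month contrast.

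The rates above are also not rates of false efficacy claims. With a 0.10 m/s deficit at 1 month, the baseline–1 pair or the 1-month t-test shows the intervention significantly worse in 91% to 98% of simulated trials. Among trials in which the 1–3 pair favours the intervention, 95% to 98% also carry that warning; with a 0.05 m/s deficit it is 65% to 76%. An attentive reader would usually see the early harm. Nothing in the article predicts such a deficit, and 0.10 m/s is the full difference on which the trial was sized.

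The predicted pattern should not be overstated either. If the benefit is 0.05, 0.10 and 0.05 m/s at 1, 3 and 12 months, the 3–12 pair turns significant against the intervention in only about 29% (r = 0.5) to 44% (r = 0.7) of trials.

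One could add that naming a deciding contrast is a detail left to an analysis plan. That does not dispose of the point. The article does more than stay silent: it states which test comes first, what that test is for, the full post hoc set and the significance rule. A later plan would have to change these statements.

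**Conclusion.** The concern holds in a limited form. The stated first-line test addresses a hypothesis other than the primary objective, and four of the six post hoc pairs (baseline–1, 1–3, 1–12 and 3–12 months) do not test benefit at 3 or 12 months. The planned contrasts that do test it rank no higher than the rest.

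The size depends on the assumed correlation, complete data and a hypothetical 1-month-only difference. The direction of the argument does not: at every correlation examined, the omnibus responds to month 1 as strongly as to a target visit. The fault is one of precedence and interpretation. It is not an absence of suitable tests, and the sample size is not in dispute.

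**What to change.** In the Data management and analysis section:

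1. State that efficacy is judged only on the between-group contrasts at 3 months and at 12 months, reported with 95% CIs. Say whether each is the change from baseline or the same-visit comparison, since both are planned. Carry the same rule into the rank-based fallback.
2. Fix an alpha rule across the two contrasts, for example Holm, or 3 months tested first and then 12 months. Without one, the chance that at least one rejects when there is no difference at either visit is about 9%.
3. Make the four-visit interaction and the baseline–1, 1–3, 1–12 and 3–12 month pairs descriptive of the recovery profile, with no efficacy claim attached. Report the 1-month contrast separately as an early-recovery result.

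This is a wording change and needs no new data or patients. It is best made before the interim analysis planned for the end of recruitment. The cost is that the omnibus and slope P values can no longer be cited as evidence of efficacy, with a small loss of power if alpha is split.

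### The four-visit repeated-measures ANOVA drops every patient with a missed visit, and intention-to-treat as the protocol defines it does not prevent this

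*Protocol article*

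**What the plan says.** All of this stands in the protocol article under Data management and analysis unless noted.

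- **Method.** "With normally distributed variables, the analysis of variance for repeated measures (AnovaRM) with two factors (time × group) will be employed". The time points are "represented by preoperative measurements (on admission to the hospital) and measurements 1, 3, and 12 months postoperatively", four in all, and the purpose is stated as "AnovaRM will be used to analyze between-group differences in the score changes among all time points".
- **Software.** "The software program SPSS 21 (IBM SPSS Statistics for Windows, version 21.0. Armonk, NY: IBM Corp.) will be used for statistical analysis".
- **Further tests.** After the four-visit ANOVA, the section plans time-by-group ANOVAs on every pair of time points, paired t-tests within groups, and independent-samples t-tests between groups at each time point. If normality is rejected, a nonparametric marginal model replaces the ANOVA.
- **Intention-to-treat.** It is introduced as "an analytic strategy for reducing potential bias in treatment effects arising from missing data in randomized controlled trials" and then defined: "a study participant is analyzed as belonging to whatever treatment group he/she was randomized into, whether or not the treatment course was completed as intended".
- **Missing data.** The one further provision is "In case of missing data, sensitivity analyses will be performed and reported". No imputation and no likelihood-based model is stated for the main analysis.
- **Sample size calculation.** It gives 124 per group for a difference of 0.10 m/s and an SD of 0.28 m/s, at a 5% significance level and 80% power. No allowance for dropout is stated.

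**The concern.** Two statements in one section do not fit together. The section expects intention-to-treat to reduce bias from missing data, but its own definition settles only which arm a patient is counted in. It does not say what happens when an outcome value is absent. The chosen test does settle that, by leaving the patient out.

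Three things are at stake:

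- **Patients lost.** A patient seen at baseline, 1 and 3 months who misses 12 months contributes nothing to the four-visit test. The Objectives name 3 months and 1 year, and the Discussion expects the largest difference at 3 months.
- **Different patients in different tests.** The four-visit ANOVA, the two-visit ANOVAs and the single-visit t-tests can each rest on a different set of patients. They may then disagree for reasons unrelated to treatment.
- **A stronger assumption than the text suggests.** A complete-case test is safe only if completers represent all randomised patients in the respects that matter. Readers told that the analysis is intention-to-treat will not expect that condition.

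**Working it through.** **1. Reproduce the planned size.** Inputs are from Sample size calculation; the test is two-sided, from Data management and analysis.

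n per arm = 2 × [SD × (z₀.₉₇₅ + z₀.₈₀) / difference]² = 2 × [0.28 × (1.960 + 0.842) / 0.10]² = 123.07, rounded up to 124. This matches the protocol.

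Power at n per arm = Φ[0.10 / (0.28 × √(2/n)) − 1.960]. At n = 124 this is Φ(2.812 − 1.960) = 80.3%. The figure requires all 248 patients to contribute.

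**2. What each planned test needs from a patient.**

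| Test | Values needed |
|---|---|
| Four-visit ANOVA | baseline, 1, 3 and 12 months |
| Two-time-point ANOVA, paired t-test | the two visits compared |
| Independent-samples t-test | one visit |

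**3. Patients remaining.** The document gives no missing-data rate, so the rates below are assumptions. Baseline is taken as complete, and each of the three post-operative visits is missed independently with probability q. Counts are rounded down.

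| q | Complete share (1 − q)³ | Four-visit test, per arm | Single visit, per arm | Single-visit power |
|---|---|---|---|---|
| 0 | 1 | 124 | 124 | 80% |
| 5% | 0.857 | 106 | 117 | Φ(2.732 − 1.960) = 78% |
| 10% | 0.729 | 90 | 111 | Φ(2.661 − 1.960) = 76% |

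The power column is for the planned two-group comparison at one visit. Power of the four-visit interaction test was not computed. It would need the correlations between visits and the pattern of effect over time, which the document does not give.

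**4. Sensitivity to the missingness pattern.** At the same per-visit rates, the completer count depends on how the misses cluster.

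- If the same patients miss all three visits, the complete share is 1 − q: 124 × 0.95 = 117 or 124 × 0.90 = 111 per arm. The four-visit test then loses no more than a single-visit test.
- If no patient misses more than one visit, the share is 1 − 3q: 124 × 0.85 = 105 or 124 × 0.70 = 86 per arm.

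The range is therefore 105 to 117 per arm at 5%, and 86 to 111 at 10%. Independence (106 and 90) lies near the unfavourable end.

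**5. Is bias shown?** No. In one simulated scenario, intervention patients who were slow at 1 month tended to miss 12 months (about 17% of all patients missing). The correlation between any two visits was assumed to be 0.6. The complete-case difference in change from baseline to 12 months averaged 0.103 m/s and a likelihood-type estimate 0.102, against a true 0.10. Equal correlations make the 1-month value unrelated to that change, so this is a benign case. It shows that bias is not automatic. It does not show that bias is absent under other patterns.

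**The case against.** The strongest reply is that the plan does not stop at the four-visit test. Patients with baseline and 3-month values enter the two-time-point ANOVA, and anyone seen at 3 months enters the t-test at that visit. These comparisons bear most directly on the Objectives. This stands, and it limits the point to the four-visit test and to the shifting patient sets.

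Three stronger readings are tempting and are not supported:

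- **That power falls to about 74% or 67%.** Those values come from putting 106 or 90 per arm into the single-visit formula. That combines the completer count of one test with the power formula of another. The single-visit t-test is not restricted to four-visit completers.
- **That the comparison is biased towards patients who coped.** The intervention section makes severe pain a reason to stop training and call the physiotherapist, not to miss an assessment. Trial status says that COVID-19 delayed recruitment and reports no missed visits. Follow-up visits are routine, with phone calls to all patients. Outcome-related missingness is plausible but not documented.
- **That the whole efficacy analysis is complete-case.** No analysis is labelled primary, the ANOVA applies only to normally distributed variables, and the nonparametric fallback is a different method outside this point.

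It can also be said that imputation and the details of sensitivity analyses may sit in an unseen analysis plan. That is fair, and the conclusion is conditional on it. It does not excuse the intention-to-treat sentence, which is wrong as written, or the choice of model, which the article itself fixes. Deletion of incomplete patients is a property of the method rather than a statement in the text, but nothing stated here counteracts it.

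**Conclusion.** The point holds in limited form. The four-visit repeated-measures ANOVA is a complete-case analysis unless imputation is added, and the protocol's account of intention-to-treat promises a protection that its own definition does not supply. The planned sensitivity analyses are unnamed and leave this test unchanged.

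Under the assumed independent misses, the four-visit test would use 106 rather than 117 per arm at 5%, or 90 rather than 111 at 10%. The gap narrows, and can vanish, if the same patients miss several visits. For the comparison that was powered, the cost is about 2 to 4 percentage points (80% to 78% or 76%), and any analysis of observed data at that visit has the same reduced numbers. Loss of patients from the four-visit test is certain once a visit is missed; bias is only possible and depends on the reasons. This should be fixed before the data are analysed, but it does not undermine the trial's design.

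**What to change.** 1. Correct the intention-to-treat sentence: it means analysis of all randomised patients in their assigned arm, and missing values are handled separately.
2. In both the protocol and the analysis plan, replace the four-visit and two-visit ANOVAs with a linear mixed model for repeated measures on all available post-operative values in the assigned arm. Include visit, arm, arm-by-visit, baseline value and hospital. Take the 3- and 12-month differences between arms as contrasts from this model, so that both come from one set of patients. The model keeps patients with some missed visits and is valid if missingness depends only on observed data. Pre-specified multiple imputation would be an acceptable alternative.
3. Name at least one sensitivity analysis for data missing not at random, for example one that shifts the missing values by a stated amount in each arm.

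The cost is a protocol wording change and a little more analysis work. The MIXED procedure in SPSS fits the model, no new data are needed, and recruitment was still open at submission according to Trial status. Changing the analysis plan alone would leave it in conflict with the protocol, where the ANOVA is written.

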**Methods/design:**

This study is a prospective multicenter randomized clinical trial to be conducted in the orthopedic departments of two Slovenian hospitals. In each hospital, 124 patients aged 60 or older with unilateral osteoarthritis, an ASA score between 1 and 3, a signed informed consent form, and no terminal illness disabling rehabilitation participation will be randomly assigned to the intervention or control group. THA with an anterior approach will be performed. All patients will receive current standard physiotherapy during hospitalization. Patients in the intervention group will also learn strength and sensory-motor training exercises. Upon discharge, all will receive USB drives with exercise videos, written exercise instructions, and a training diary. Physiotherapists will perform the assessments (physical tests and the maximal voluntary isometric contraction assessment), and patients will fill out outcome assessment questionnaires (the Harris Hip Score and 36-Item Short Form Health Survey) at baseline and 1, 3, and 12 months after surgery.

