#### Sample size calculation

A power calculation was performed based on a clinically significant difference in gait speed of 0.10 m/s on the 4- or 10-m walk (10 MW) test using data from Perera et al. [32]. Based on a substantial meaningful change of 0.10 m/s between the interventional and control groups and standard deviation of 0.28 m/s, with a significance level of 5% and a power of 80%, a needed sample size of 124 patients in each group was estimated (248 patients in total). All patients from surgeons, participating in the study, will be assessed for eligibility. A total of 124 patients in each hospital will be randomized according to the procedure described above on a 1:1 ratio, so that there will be 62 patients in group A and group B in both hospitals.

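### The planned between-group tests never adjust for the preoperative value, which gives up power at no saving

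*Protocol article*

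**What the plan says.** Data management and analysis names the tests for normally distributed outcomes:

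- A repeated-measures ANOVA with time and group as factors over the preoperative, 1-, 3- and 12-month values, used to "analyze between-group differences in the score changes among all time points".
- Post hoc ANOVAs of the same form on every pair of time points.
- Independent-samples t-tests "for between-group comparisons at the same time point will be calculated".

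The nonparametric substitutes (nparLD, Mann–Whitney) follow the same pattern. No covariate is named for any of them. The abstract states that outcomes are assessed "at baseline and 1, 3, and 12 months after surgery", so the preoperative value is scheduled for every patient.

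The section Sample size calculation is a plain two-group calculation: "Based on a substantial meaningful change of 0.10 m/s between the interventional and control groups", with a "standard deviation of 0.28 m/s", 5% significance and 80% power, giving 124 per group. It mentions no correlation between visits. The analysis section adds: "A significance level (alpha) of 0.05 will be tested with a two-tailed test".

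**The concern.** With two groups and two time points, the time × group interaction is algebraically a t-test on the change from one visit to the other. The planned pairwise tests involving baseline are therefore change-score tests, and the same-visit t-tests ignore baseline altogether. With equal variances at the two visits, adjusting for baseline as a covariate is more precise than either for any correlation strictly between 0 and 1. The change-score test is less precise than ignoring baseline when the correlation is below 0.5. A low correlation is conceivable here, because surgery replaces the joint that limits preoperative performance, but the article gives no figure.

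The stated power belongs to a simple two-group comparison. It does not carry over automatically to the repeated-measures ANOVA that leads the analysis, or to its change-score follow-ups. The four-visit interaction asks whether the two curves differ in shape anywhere. It does not itself estimate the difference at 3 months or at 1 year, which is what the objectives name.

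**Working it through.** **Inputs from the article.** Difference 0.10 m/s; SD 0.28 m/s; two-sided alpha 0.05; 124 per group, allocated 1:1.

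**Inputs assumed.** The correlation r between the preoperative and follow-up value, shown at 0.3, 0.5 and 0.7; equal SDs at all visits; no dropout. The article does not say whether 0.28 is the SD at one visit or the SD of change, so both readings are worked.

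**Step 1: reproduce the plan's figure.** n per group = 2 × (1.960 + 0.842)² × 0.28² / 0.10² = 123.1, rounded up to 124. Power of a two-sample t-test at 124 per group is 80.0% by the noncentral t (80.3% by the normal approximation). The stated sample size is correct for an unadjusted two-group comparison.

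**Step 2: 0.28 as a single-visit SD.** The effective SDs are:

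- unadjusted follow-up value: 0.28
- change score: 0.28 × √(2(1 − r))
- ANCOVA: 0.28 × √(1 − r²)

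Power at 124 per group (noncentral t), effective SD in brackets:

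| r | Change score | Unadjusted | ANCOVA |
|---|---|---|---|
| 0.3 | 65.8% (0.331) | 80.0% (0.280) | 83.6% (0.267) |
| 0.5 | 80.0% (0.280) | 80.0% (0.280) | 89.9% (0.242) |
| 0.7 | 95.1% (0.217) | 80.0% (0.280) | 97.5% (0.200) |

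In terms of patients, 80% power with ANCOVA needs 112, 93 and 63 per group at these r, against 173, 124 and 74 for the change score (normal approximation).

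**Step 3: 0.28 as the SD of change.** The single-visit SD is then 0.28 / √(2(1 − r)), and the ANCOVA SD is that value × √(1 − r²), which simplifies to 0.28 × √((1 + r)/2).

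| r | Change score | Unadjusted | ANCOVA |
|---|---|---|---|
| 0.3 | 80.0% (0.280) | 91.2% (0.237) | 93.5% (0.226) |
| 0.5 | 80.0% (0.280) | 80.0% (0.280) | 89.9% (0.242) |
| 0.7 | 80.0% (0.280) | 58.3% (0.361) | 86.0% (0.258) |

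On both readings ANCOVA has the highest power in every row. Which of the two planned tests does worse depends on the reading and on r.

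**Step 4: the four-visit interaction.** I assume single-visit SD 0.28 and the same correlation r between all visits. The noncentrality is (124/2) × Σ(d − d̄)² / (0.28² × (1 − r)), with 3 and 738 degrees of freedom, where d holds the group differences at baseline, 1, 3 and 12 months.

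| Differences (m/s) | Σ(d − d̄)² | r = 0.3 | r = 0.5 | r = 0.7 |
|---|---|---|---|---|
| 0, 0.05, 0.10, 0.05 | 0.0050 | 49% | 65% | 87% |
| 0, 0.10, 0.10, 0.10 | 0.0075 | 68% | 83% | 97% |

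The Discussion predicts the largest difference at 3 months but gives no sizes for the other visits. Both rows are illustrations.

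**The case against.** The strongest reply is that nothing planned is invalid. Under randomisation the change-score and same-visit comparisons both estimate the treatment effect without bias, and the sample size arithmetic is right. If 0.28 is a single-visit SD, the same-visit t-test has exactly the power that was promised. All of that stands.

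Three stronger readings are tempting, and the document does not support them.

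- *The trial is underpowered.* A shortfall in the change-score test needs r below 0.5 and 0.28 to be a single-visit SD. The article gives neither. At r = 0.7 on that reading the test has 95% power, and if 0.28 is the SD of change it has 80% by construction.
- *The omnibus test has only about half the power it should.* The 49% comes from one assumed pattern at the lowest correlation shown. Across the two patterns and three correlations the range is 49% to 97%.
- *The unadjusted tests are biased by chance imbalance.* They are not biased over repeated randomisations. Adjustment accounts for the imbalance in the sample actually drawn, and that is a gain in precision.

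It can also be said that the pairwise and same-visit tests do examine the 3- and 12-month differences. They do, but without adjustment. Which of them should be primary is a separate question.

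**Conclusion.** The point holds as a loss of efficiency. For continuous outcomes, every between-group test the article names leaves out baseline as a covariate, although baseline is scheduled for every patient. With 0.28 as a single-visit SD, ANCOVA gains about 4, 10 and 17.5 percentage points over the unadjusted t-test at r = 0.3, 0.5 and 0.7, and about 18, 10 and 2 points over the change-score test. With 0.28 as the SD of change, it gains 13.5, 10 and 6 points over the change-score test. The direction is certain for any r strictly between 0 and 1 with equal variances; the size rests on r, which is assumed. That the power of a planned test falls below 80% is a possibility under stated conditions and cannot be established from the article.

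**What to change.** Amend Data management and analysis so that the between-group comparison at 3 months and at 12 months is an ANCOVA, or a linear mixed model of the follow-up visits, with the patient's own preoperative value of that measure as covariate. Report each as an adjusted mean difference with a 95% CI. Keep the repeated-measures ANOVA, the change-score post hoc tests and the same-visit t-tests as supportive or descriptive only. In Sample size calculation, state whether 0.28 m/s is a single-visit SD or the SD of change.

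No further patients, visits or measurements are needed. The cost is a dated amendment to published tests. Recruitment was still open when the article was submitted, and Data monitoring plans an interim analysis once recruitment is complete, with results shown to the thesis committee. The amendment should be dated before that analysis, so that the choice of model is made before comparative results are seen.
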